
As the effects of a single session of cTBS are thought to be transient (on the order of minutes to less than 2 hours in duration), the goal of this study is to evaluate target engagement and the acute effects of cTBS on auditory/language network functioning. Thus, the cTBS session is administered within the Functional Magnetic Resonance Core Facility at the National Institutes of Health in Bethesda, Maryland, USA allowing for acquisition of imaging measures both immediately before and immediately after each cTBS session. We do not expect to induce an observable clinical/behavioral change, however, questionnaires are administered at the end of each session to assess for any observable changes in behavior or other side effects reported by participants. If successful, this study may inform future therapeutic trials aiming to treat the symptoms of ASD by modulating network functioning through pharmacological or device-based manipulations of glutamate and/or GABA concentrations; however, to induce such long-lasting clinical effects, multiple sessions of cTBS or multiple doses of a pharmacologic agent would be required.

Of note, Ni and colleagues recently applied intermittent theta burst stimulation (iTBS) to bilateral posterior superior temporal sulci (pSTS) in adults with ASD and showed improvements in parent-reported ASD symptoms and compulsive behaviors (as measured by AQ and Y-BOCS scales) (76, 77), but no change in white matter macro/micro structure (78). However, when the same group applied cTBS to the dorsolateral prefrontal cortex (DLPFC), they did not find any significant improvement (as compared to sham stimulation) in executive functioning symptoms in a recently published study of children, adolescents, and adults with ASD (79). Taken together with the literature on aberrant functioning of the pSTC region and its relationship to ASD symptoms described above, Ni and colleagues findings suggest that the pSTC may be a better putative target than the DLPFC for future rTMS studies in ASD. Experimental therapeutics approaches and proof of mechanism studies such as the one described in the current paper will provide evidence for target engagement to guide the development of optimal parameters and protocols for future rTMS studies in ASD.

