### Study design

2.1

This study employs a within-subject crossover design whereby participants receive both active and sham cTBS on different days based on a randomized blinded code that is entered into the TMS machine before each session. The crossover design was chosen because of the documented heterogeneity of neuroimaging outcomes within the ASD population as well as the interindividual variability in response to cTBS and other rTMS protocols. Therefore, it was determined that a between-subject design would be less powerful in determining the acute effect of cTBS on these neuroimaging outcomes.

Participants, study staff members and all other study personnel involved in TMS administration, data collection, or data analysis are blinded to whether sham or active stimulation is delivered during each cTBS session.

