### Power analyses and sample size determination

2.3

The first aim of the study is to establish the relationship between local GABA and glutamate neurotransmitter concentrations, structural and functional network connectivity, and physiological measures of auditory/language network functioning. The estimated effect size for this aim is approximately 0.2223. This is estimated based on the literature showing a significant correlation between GABA+/Cre concentration and MEG evoked gamma power that range from 0.37-0.53 (49, 52, 56, 80). To our knowledge there is not any existing data on the correlation between the other predictor variables (DWI or functional MR connectivity) and MEG power and latency of evoked fields. However, given that both of these neuroimaging predictor variables have been shown to be aberrant in adolescents with ASD and reflect network-level structural and functional dysfunction, we predict a correlation between these neuroimaging measures and the proposed MEG measure of at least 0.15. Thus, in order to maintain 80% power with a type-I error rate of 5% and a type-II error rate of 20% we will enroll 86 ASD participants with a planned evaluable N=55 accounting for attrition.

The second aim of the study is to evaluate target engagement and the acute effects of active cTBS compared to sham cTBS on auditory/language network functioning. With planned evaluable N=55 and the minimal detectable effect (given Lehr’s equation (81)), the minimum detectible effect size is 0.38 standard deviation units, between a small (.2) and medium (.5) effect size in Cohen’s effect size taxonomy (82). We believe this is a reasonable effect size to expect given the literature. A recent study found an effect size of 0.7 on MRS GABA+/Cre concentration and 0.39 on MEG indices of sensory (visual) processing immediately following a single session of cTBS [95]. Therefore, we believe this aim is adequately powered.

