##### MEG

2.4.4.1

Data is converted to MEG-BIDS (108) format using MNE-BIDS toolbox (109) and is analyzed with MNE-Python toolbox (110) for electrophysiological research, Freesurfer (111) for anatomical surface preparation, and custom scripts written in Python and Bash. The raw MEG data sets (baseline, and post stimulation for active TBS and sham TBS) for each participant undergo quality control procedures to remove trials corrupted by artifacts. Broadband evoked responses are extracted, as well as induced changes in oscillatory power in the time frequency response. Data are analyzed in both sensor space and anatomical source space. Forward modeling of the down-sampled cortical manifold is assessed using a realistic single layer boundary element model and source localization is performed using beamformer or minimum norm techniques, depending on the task. For evoked responses, source localized time series amplitude and latency (defined as the time interval between stimulus and maximal amplitude) are determined. For induced power analyses, the peak induced gamma frequency will also be determined. In the context of the M100/M50 task, two components are identified – the M50 and the M100, both occurring in Heschl’s gyrus, in left and right superior temporal cortices. In the speech processing oddball paradigm, the mismatch negativity is identified as the difference between the evoked responses to the frequent and rare tones. For the auditory steady state experiment, inter-trial coherence is calculated as described in (112).

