##### MRS

2.4.4.2

Custom software is used to measure the relative concentrations of metabolites (N-acetylaspartate, creatine plus phosphocreatine, choline-containing compounds, GABA, and glutamate/glutamine) and metabolite ratios. The data is pre-processed with an eddy current correction and the data is tested for patient movement by tracking the residual water signal, edit - non edit pairs with residual water deviations larger than 10% are rejected (45). Subsequently, the averages of the data are frequency and phase corrected before summation (113). In a last step, the summed data is fitted with simulated reference signals for the non-edited, the edited, and the subtracted data (113). Standard statistical packages such as Statistica are used to determine significant differences in the metabolites taken immediately prior to and immediately following cTBS administration. In-house software was written to derive ratios of GABA and glutamate to creatine.

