### Statistical analysis

2.5

Multiple linear regressions will be conducted to evaluate whether baseline MRS measures of local GABA and glutamate concentration, structural topography/connectivity, and/or functional activity/connectivity explain a significant proportion of the variability in MEG measures of auditory/language processing. These analyses will quantify the relationship between these measures and to what extent they may contribute to a fusion biomarker model for language processing deficits in ASD (e.g., (139)). To evaluate the effect of a single session of cTBS on MRS, fMRI, and MEG outcome measures, Factorial ANCOVAs will be conducted with time-point (pre-post) and condition (active, sham) as within-subjects variables. Other anticipated covariates in these analyses include age, gender, baseline symptom severity, and medication use. In addition to the targeted region (left pSTC), we will repeat the planned fMRI BOLD and connectivity analyses using right pSTC, left and right IFG, and a non-connected (control) cortical visual network with a temporal and frontal node to explore the spread of the effect of the cTBS from the targeted region to other structurally and functionally connected regions compared to a control network. Pearson correlation coefficients will be used for the exploratory analyses, to characterize the relationship between the neuroimaging and electrophysiological indices and baseline behavioral symptom presentation including assessments of general functioning, autism symptom severity, and auditory and language processing. As there may be intrasubject variability in these measures (independent of the cTBS intervention), we will evaluate the reliability of the baseline/pre-stimulation MEG, MRS, and fMRI outcomes by calculating the interclass correlation coefficient (Model: 2-way mixed effects, Type: mean of k measurements and Definition: absolute agreement) as a measure of test-retest reliability.

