**Figure 6 f6:**
[figure not shown]
Pre-post cTBS changes in M100 latencies significantly correlated with pre-post cTBS changes in glutamate/GABA ratios at baseline during the pilot phase. Notably, these changes occurred in the predicted direction, where a decrease in the ratio of glutamate/GABA was observed for individuals who experienced a decrease in M100 latency.

The pilot phase was not powered to achieve significance in these measures, however, the significant findings presented above provide preliminary data supporting our hypothesis of a relationship between measures of local neurochemical concentrations, structural/functional connectivity of the network, and MEG measures of auditory processing and the impact of a single session of cTBS on these measures. Brain functioning in typical development is presumably optimized, making further improvement or speed of basic auditory and language network functioning difficult to achieve (ceiling effect). Thus, there may have been a limit to how much gamma power could be evoked by the MEG task or how functionally connected a network could be during the fMRI task. Additionally, the directionality of these findings (positive versus negative relationships) may be different in the ASD group compared to this typically developing pilot sample.

In the ASD group, we hypothesize that the auditory and language networks are not optimized, thus, there will be more opportunity for modulation in these individuals (i.e., a ceiling effect is not expected in the ASD group). Based on these preliminary findings as well as the extant literature, we anticipate that baseline MRS glutamate and GABA concentrations, DWI measures of tissue microstructure, and task-related functional connectivity will be significant predictors of MEG indices of auditory/language processing in adolescents with ASD. Furthermore, we hypothesize that a single session of active cTBS compared to sham cTBS over the individually targeted region of the pSTC will lead to significant decreases in the glutamate/GABA ratio as measured by MRS, significant modulation in task-related functional connectivity within the fronto-temporal language network, and significant modulation in MEG indices of auditory/language processing in the direction of more efficient processing.

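### The Aim 2 test of cTBS is a difference of two change scores; adjusting for each session's own pre-scan would be equally valid and usually more precise

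*Protocol article*

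**What the plan says.** The design is a crossover: "This study employs a within-subject crossover design whereby participants receive both active and sham cTBS on different days" (section 2.1). The Introduction describes the setting as "allowing for acquisition of imaging measures both immediately before and immediately after each cTBS session", so every cTBS session has its own pre-scan.

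Section 2.5 gives the Aim 2 model: "Factorial ANCOVAs will be conducted with time-point (pre-post) and condition (active, sham) as within-subjects variables". On covariates it adds: "Other anticipated covariates in these analyses include age, gender, baseline symptom severity, and medication use". The session's own pre-scan is not among them. The hypothesis in section 3 is comparative: "we hypothesize that a single session of active cTBS compared to sham cTBS over the individually targeted region of the pSTC will lead to" changes in the MRS, connectivity and MEG measures.

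Section 2.3 gives a minimum detectable effect of 0.38 SD units for Aim 2 at 55 evaluable participants, from Lehr's equation. It does not say which SD is meant.

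Two image-processing sections touch the same data in looser terms. Section 2.4.4.1 refers to "The raw MEG data sets (baseline, and post stimulation for active TBS and sham TBS) for each participant". Section 2.4.4.2 speaks of software used to "determine significant differences in the metabolites taken immediately prior to and immediately following cTBS administration".

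**The concern.** Making pre and post two levels of a within-subject factor puts the pre-scan on the outcome side. The article does not name the time-by-condition term, but in this model that term is the active-versus-sham test of change. It equals (post − pre) under active minus (post − pre) under sham.

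In a crossover the participant's stable level already cancels between active and sham. Subtracting the pre-scan as well helps only to the extent that two scans of one session share something that scans on different days do not. Otherwise the subtraction adds the pre-scan's own noise. The named covariates cannot make up for this: they describe the participant, are the same for both sessions, and leave session-to-session noise in the contrast untouched.

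At stake is precision on the Aim 2 outcomes, using data the trial already collects. The margin in section 2.3 is thin: a detectable effect of 0.38 is set beside a literature effect of 0.39 for an MEG measure.

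**Working it through.** **Inputs from the article.** Evaluable N = 55 and detectable effect 0.38 SD (section 2.3). Alpha of 5% and power of 80% are stated there for Aim 1 and are taken, two-sided, for Aim 2. The covariates are those of section 2.5.

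**Inputs assumed.** Equal variance of pre and post scans, and r from 0 to 0.9. No correlation is given in the article.

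**Step 1: the plan's own figure.** Lehr's equation in paired form gives √(8/55) = 0.381, which matches 0.38. The two-sample form, √(16/55) = 0.539, does not. An exact paired t-test at 0.38 with N = 55 has 79.0% power. So 0.38 is arithmetically sound and refers to a paired contrast; which one is not said.

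**Step 2: the two variances.** Let D0 = pre(active) − pre(sham) and D1 = post(active) − post(sham), each with variance V, and corr(D0, D1) = r.

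- Planned contrast, D1 − D0: V + V − 2rV = 2(1−r)V.
- D1 adjusted for D0 by regression: (1−r²)V = (1−r)(1+r)V.
- Ratio: 2(1−r) / [(1−r)(1+r)] = 2/(1+r).

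If scans of one session correlate at ρw and scans of different sessions at ρb, then r = (ρw − ρb)/(1 − ρb). So r = 0 means that two scans in one visit agree no better than scans from different visits.

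**Step 3: numbers.** A simulation of 20,000 trials at N = 55 checks the formula. The fourth column is 55 × 2/(1+r), rounded up: the evaluable N at which the planned test matches the adjusted one at 55.

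| r | 2/(1+r) | simulated | N to match |
|---|---|---|---|
| 0 | 2.00 | 1.97 | 110 |
| 0.5 | 1.33 | 1.31 | 74 |
| 0.7 | 1.18 | 1.15 | 65 |
| 0.9 | 1.05 | 1.04 | 58 |

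The simulated ratios are slightly lower because the slope has to be estimated. That costs a factor of 1 + 1/(55−3) = 1.019, about 2%. Setting 2/(1+r) equal to 53/52 gives r = 104/53 − 1 = 0.96. Above that, adjustment would be marginally worse.

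**Step 4: power at N = 55.** This depends on the SD behind 0.38. The powers below use the large-sample ratio and do not deduct the 2%.

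| r | 0.38 in SDs of the planned contrast: planned → adjusted | 0.38 in SDs of the adjusted contrast: power of the planned test |
|---|---|---|
| 0 | 79% → 97.5% | 50% |
| 0.5 | 79% → 89% | 67% |
| 0.7 | 79% → 85% | 72% |
| 0.9 | 79% → 81% | 77% |

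In the middle column the standardised effect becomes 0.38 × √(2/(1+r)), for example 0.38 × 1.155 = 0.439 at r = 0.5. In the last column it is 0.38 divided by the same root.

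**The case against.** **It is a valid, standard model.** True. The interaction test is unbiased under randomisation, and the covariate list is worded as open. A reader might infer that the planned analysis is wrong; it is not. The point is only that a better estimator is available from the same scans.

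**A factor of two is the boundary.** Also true. It needs r = 0. Pre and post scans are taken around one stimulation within a visit, while visits are about a week apart, so some positive r is plausible. At r = 0.7 or above the ratio is 1.18 or less. Section 2.5 itself allows for variability within participants unrelated to cTBS and plans to measure reliability, so r near 1 cannot be taken for granted either.

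**Underpowering is not shown.** This stands. A reader might infer from the last column of step 4 that Aim 2 is underpowered. That requires 0.38 to be in SDs of the adjusted contrast, which the article does not say. If it is in SDs of the planned contrast, the plan already has about 79%.

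**The processing sections.** A reader might infer from section 2.4.4.1 that MEG has no per-session pre-scans, or from section 2.4.4.2 that MRS is tested before against after without sham, so that scanner drift could pass for a cTBS effect. The documents do not support this. The Introduction places imaging before and after each session, section 2.5 applies the active/sham model to MRS, fMRI and MEG alike, and section 3 states the glutamate/GABA hypothesis against sham. These are loose processing sentences overridden by the statistical section. If a single MEG baseline really served both conditions, it would cancel from the active-sham contrast and the efficiency argument would not apply to MEG.

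**Missing scans.** Regressing the differences needs all four scans of a modality, but so does a difference of two changes. This does not favour the planned test.

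**Conclusion.** The point holds as lost efficiency, not bias. The planned active-versus-sham test has 2/(1+r) times the variance of a contrast adjusted for the session's own pre-scan: between 2.0 and 1.05 as r runs from 0 to 0.9. This rests on equal pre and post variances and on a range for r that is assumed. The corresponding gain in power at N = 55, from about 79% to between 81% and 97.5%, further assumes that 0.38 is in SDs of the planned contrast. The 0.38 itself reproduces and is not in error. The change is worth making because estimating the slope adapts to whatever r turns out to be, at almost no cost.

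**What to change.** In section 2.5, make the Aim 2 test the active-sham difference in the post-stimulation value, adjusted for the pre-stimulation difference. Either regress post(active) − post(sham) on pre(active) − pre(sham), with the intercept as the cTBS effect, or fit an equivalent mixed model with the session pre value and the participant's mean pre value as covariates. In section 2.3, name the SD to which 0.38 refers.

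As wording alignment only, let sections 2.4.4.1 and 2.4.4.2 match section 2.5: pre and post data sets for each cTBS session, compared between active and sham.

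The cost is a change of text with no new scans or visits. Analysts are blinded and recruitment is described as under way, so the change can be made before any unblinded result is seen. The statistical downside is about 2% in variance at N = 55 for estimating the slope, and almost no gain if r is near 1.

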**Figure 1 f1:**
[figure not shown]
Schematic depicting the study protocol. After enrollment, participants complete screening, including an audiometric assessment and neuropsychological evaluation only for the individuals with ASD [Healthy Volunteer (HV) participants receive an abbreviated Neuropsychological Evaluation]. Baseline imaging was then conducted, and participants were randomized to either complete MEG/TMS or MRI/TMS sessions first and then within the session randomization active or sham (for ASD participants only) first. For example – MEG/active TMS, MEG/sham TMS, MRI/sham TMS, MRI/active TMS. * indicates procedures only completed by ASD participants. ** indicates procedures that differed between HV participants and ASD participants.

**Table 1 T1:** Demographics for the Healthy Volunteer sample in the pilot phase.

N (Male/Female)	20 (5/15)
Age, years (Mean ± SD)	23 ± 0.94
FSIQ (Mean ± SD) SRS-2 Total T score (Mean ± SD) SRS-2 SCI T score (Mean ± SD) SRS-2 RRB T score (Mean ± SD)	121.3 ± 13.0 (n=18) 43.26 ± 4.30 (n=19) 44.58 ± 4.07 (n=19) 43.21 ± 4.48 (n=19)

Full Scale Intelligence Quotient (FSIQ) measured by Wechsler Abbreviated Scale of Intelligence, Second-Edition (WASI-II) with a population mean of 100 and standard deviation of 15. Two participants were withdrawn prior to completing this assessment. Social Responsiveness Scale, Second Edition (SRS-2) T scores are presented for the total scale, Social Communication Subscale (SCI), and Restrictive and Repetitive Behaviors Subscale (RRB). SRS-2 Total T scores of 59 and below are considered to be within typical limits.

**Table 2 T2:** Baseline imaging measures for the Healthy Volunteer sample in the pilot phase.

Region	Measurement	Mean ± SD
Left pSTC	GABA/Cre Concentration (mmol/L)	0.54 ± 0.05 (n=10)
	Glutamate/Cre Concentration (mmol/L)	1.25 ± 0.13 (n=10)
Left Heschl’s Gyrus	Evoked Gamma Power	0.32 ± 0.38 (n=13)
	M100 Latency (ms)	98.4 ± 9.9 (n=10)
Right Heschl’s Gyrus	Evoked Gamma Power	0.48 ± 0.36 (n=13)
	M100 Latency (ms)	97.6 ± 7.7 (n=9)
Left Arcuate Fasciculus	FA	0.45 ± 0.01 (n=19)
	MD	0.76 ± 0.01 (n=19)
	RD	0.55 ± 0.02 (n=19)
	AD	1.14 ± 0.02 (n=19)
Right Arcuate Fasciculus	FA	0.45 ± 0.02 (n=19)
	MD	0.75 ± 0.04 (n=19)
	RD	0.55 ± 0.02 (n=19)
	AD	1.13 ± 0.02 (n=19)
Left Auditory Radiations	FA	0.39 ± 0.01 (n=19)
	MD	0.89 ± 0.04 (n=19)
	RD	0.71 ± 0.04 (n=19)
	AD	1.26 ± 0.04 (n=19)
Right Auditory Radiations	FA	0.39 ± 0.02 (n=19)
	MD	0.88 ± 0.02 (n=19)
	RD	0.70 ± 0.03 (n=19)

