#### Continuous theta burst stimulation

2.4.3

As shown in **Figure 1**, each participant in the pilot phase completed two active cTBS sessions (one with MRI and one with MEG acquired immediately before and after stimulation). Participants in the main phase of the study will complete four cTBS sessions (two active and two sham). cTBS sessions are scheduled approximately once/week to avoid carry-over effects from one visit to the next. The cTBS protocol consists of bursts of three pulses of 50 Hz stimulation repeated at 200 ms intervals (5 times per second) for 40 seconds (for a total of 600 pulses). Stimulation is applied at an intensity of 80% of active motor threshold (AMT) defined as the minimum stimulator intensity required to elicit a motor evoked potential from the first dorsal interosseous muscle of at least 200 microvolt peak to peak amplitude on five out of ten trials while the participant maintains voluntary contraction of the target muscle. A neuronavigation system (Brainsight, Rogue Research, Canada) is used to track the position of the TMS coil over the stimulated target. The target is defined by combining e-field modeling (described below) with the participant’s peak BOLD activation within the left pSTC during the baseline ADDT task, overlaid on the structural anatomical scan. A functional localizer (rather than a single structurally-defined ROI) was used in this study as previous literature suggests significant interindividual variability in both typically developing individuals (102) as well as those with neurological disorders (103, 104). The feasibility of the application of TBS in the proposed study populations has also been well supported in the literature and by our own experience (65, 105–107).

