In the current study, cTBS is administered using a MagPro X100 magnetic stimulator (P/N: 9016E711, Magventure A/S) and a double-sided Cool-B65 Active/Placebo (A/P) coil (P/N: 9016E0501, MagVenture A/S). Inside the A/P coil, there is a figure-of-eight winding on the active side and a metal shield on the sham side, separated by approximately 8 cm. For active stimulation, the active side of the coil is placed on the scalp; for sham stimulation, the coil is flipped, and the spacer and shield attenuate the field reaching the brain. Visually, both sides of the coil are identical, therefore blinding the TMS technician to active or sham mode. During a cTBS session, a unique patient code, supplied by MagVenture, is inputted into the MagPro X100 system, which then prompts the TMS technician to either flip or maintain coil orientation. A randomized schedule of visits was created using block randomization and the unique patient codes designating active or sham mode, and is kept in an electronic password protected document by an unblinded study staff member. The order of sessions is scheduled to ensure that the participant receives active and sham stimulation for one modality (MRI or MEG) prior to moving on to the other modality. Thus, there are only four potential orders (Active, Sham, Sham, Active; Active, Sham, Active, Sham; Sham, Active, Sham, Active; and Sham, Active, Active, Sham). The block randomization ensured that there will be the same number of participants receiving the cTBS in each of these orders.

Participants are asked to complete an Assessment of Blinding following each cTBS session to assess the integrity of the blind. During the assessment, participants are asked to guess whether they received active or sham TMS and to report their confidence in their guess on a scale from 0 (not confident at all) to 5 (extremely confident). Participants are also asked to rate the loudness and painfulness of the stimulation and to describe any facial muscle twitching or additional side effects experienced during cTBS.

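### The Aim 2 ANCOVA names participant-level covariates that cannot sharpen the active-sham contrast, and does not name session or randomised order, the terms the crossover is built on

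*Protocol article*

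**What the plan says.** The Study design section of the protocol article (2.1) sets up a crossover: "This study employs a within-subject crossover design whereby participants receive both active and sham cTBS on different days". The section on continuous theta burst stimulation (2.4.3) gives the active/sham sequences, "Thus, there are only four potential orders", and says of the allocation: "The block randomization ensured that there will be the same number of participants receiving the cTBS in each of these orders". The legend to Figure 1 adds that "participants were randomized to either complete MEG/TMS or MRI/TMS sessions first". Carry-over is handled by spacing: "cTBS sessions are scheduled approximately once/week to avoid carry-over effects from one visit to the next".

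Section 2.5, Statistical analysis, states the Aim 2 model: "Factorial ANCOVAs will be conducted with time-point (pre-post) and condition (active, sham) as within-subjects variables". It continues: "Other anticipated covariates in these analyses include age, gender, baseline symptom severity, and medication use". Neither session nor randomised order is named as an analysis term there or elsewhere in the article.

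Section 2.3 gives the numbers: "we will enroll 86 ASD participants with a planned evaluable N=55 accounting for attrition". It states a minimum detectable effect for Aim 2 of 0.38 standard deviation units.

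**The concern.** The crossover was chosen so that differences between people drop out of the treatment comparison. Age, gender and baseline severity are such differences, and so is medication use unless it changes between visits. Adjusting for them does not improve a comparison from which they have already dropped out.

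Session number and order do vary in a way that can touch the contrast. The same measurements are made before and after stimulation at both visits of a modality. If habituation or practice within a visit is stronger the first time than the second, the pre-post change will differ by session whatever was delivered. Without a session term this either inflates the residual variance or, if the orders are unequal among those analysed, moves the treatment estimate. The 0.38 SD figure has no reserve for either.

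**Working it through.** **Inputs.** From the article: 55 evaluable of 86 enrolled; detectable effect 0.38 SD; 80% power and 5% type I error (stated for Aim 1, taken here as two-sided and applied to Aim 2). Assumed: the size of the session effect and the split of orders among the 55.

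**Step 1. Reproduce 0.38.** The paired form of Lehr's rule, n = 8/d², gives d = √(8/55) = 0.381. The two-sample form, n = 16/d² per group, gives √(16/55) = 0.539 and does not match. So 0.38 is in SDs of the within-participant contrast, with no session term and no covariates. A paired t-test with 55 participants has 79.0% power at 0.38.

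**Step 2. The covariates.** The contrast for participant i is

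D = (post − pre, active) − (post − pre, sham).

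Anything constant within a participant cancels. In a simulated data set of 55 participants with four cells each, a mixed model gave a time-by-condition estimate of 0.4567 (SE 0.1338) both with and without age.

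**Step 3. Whole-visit shifts.** A shift common to the pre and post scans of one visit also cancels. Adding large random visit shifts to the same data left the estimate at 0.4567.

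**Step 4. What does not cancel.** Let c1 and c2 be the mean pre-post change arising in the first and second session regardless of condition, and τ the treatment effect.

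- Active first: mean D = τ + (c1 − c2)
- Sham first: mean D = τ − (c1 − c2)

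Write π for (c1 − c2) in SDs of D. The two order groups then lie 2π apart, and π is half that gap. The assumed range is 0 to 0.5.

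**Step 5. Balanced orders (28:27), 40,000 simulated trials per setting.**

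| π | Power at 0.38, no session term | Power, with term | Type I error, no term |
|---|---|---|---|
| 0 | 79.1% | 79.1% | 5.1% |
| 0.3 | 77.6% | 78.9% | 4.2% |
| 0.5 | 73.8% | 79.1% | 2.8% |

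Without the term, the estimated variance of D rises by a factor of about 1 + π² (1.09 and 1.25). The true sampling variance of the mean does not, so the test is conservative.

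**Step 6. Unequal orders.** The share of π entering the treatment estimate is (n1 − n2)/55.

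- At an assumed 32:23 this is 9/55 = 0.16. For π of 0.3 and 0.5 the bias is 0.05 and 0.08 SD, against an effect of 0.38.
- If 55 of 86 are retained at random from a 43/43 start, a split of 32:23 or worse has a hypergeometric probability of about 7%.
- At an assumed 33:22, type I error without the term is 6.2% (π = 0.3) and 7.6% (π = 0.5). With the term it is about 5%.

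**The case against.** The strongest reply is that this argues from silence. The covariate list is open-ended, the article is condensed, and an analysis plan not shown may add session and order. Blocked orders already remove most of the bias, and the pre-stimulation scan at each visit removes visit-level drift. The 55 already allows for attrition, and some of the 31 losses may occur before randomisation, which Figure 1 places after baseline imaging; those cannot unbalance the orders. Covariates crossed with condition could also serve as moderators. The article itself expects larger effects in those with more severe symptoms, and medication use may change between visits.

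Much of this stands. It limits the size of the problem and rules out any claim that the covariates are illegitimate. It does not remove the point: the article does state a model, and that model names terms that do not help the contrast but not the terms by which the trial randomises.

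A reader might infer that adjusting for age wrecks the main test. That would need age both crossed with the within-subject factors and left uncentred, so that the test refers to age zero. The text says neither. With all four covariates crossed and centred, the loss is about one percentage point of power or less.

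A reader might also infer that exact balance is impossible because 86 is not a multiple of four. Within a modality only active-first versus sham-first matters, and 86 divides 43/43.

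**Conclusion.** The point holds in a conditional form. The named covariates, entered additively, do nothing for the active-sham contrast, and session and randomised order should be in the stated model. Omitting them does not always cost power. The loss is nil without a session effect on the pre-post change, about 1 point at π = 0.3 and about 5 points at π = 0.5 with balanced orders. Bias needs both such an effect and unequal orders among the evaluable. The planned loss from 86 to 55 makes that possible, but the article does not predict it. The values of π and the 32:23 and 33:22 splits are assumptions.

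Two wider readings are not supported. General scanner familiarity between visits does not enter the error term, because it cancels in the pre-post difference. Nor does the wording exclude age from the Aim 1 regressions, so no confounding there can be inferred. The change is worth making because it is cheap and follows the randomisation; the plan is not invalid without it.

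**What to change.** State the Aim 2 model for each modality as a linear mixed model on the pre-post change, or on the post-stimulation value adjusted for that session's pre-stimulation value. The fixed effects are condition, session (first or second in that modality) and randomised order, with a participant random effect. Use all usable sessions; this also avoids depending on complete sets of four scans, which a classical repeated-measures ANCOVA would need. Centre any covariate crossed with time or condition, or keep it for a secondary moderator analysis.

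The cost is a few sentences in the analysis plan and one or two degrees of freedom. With balanced orders, one degree of freedom leaves paired-t power at 79.0%. If the evaluable split were 33:22 and there were no session effect, adjusting would lower power from 79.1% to 77.3%. That is a modest price for a type I error that stays at about 5% whatever the session effect.
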